Cohen [42] argues that strengthening and increasing the availability of support in social networks, and reducing negative interactions within one’s network are essential for human health. Psycho-education can be a viable strategy for achieving this. Psycho-education is defined as professionally delivered illness-specific information and tools for managing challenges in everyday life [44]. It builds on a holistic and competence-based approach, focusing on health promotion, collaboration, and empowerment where the development of open communication, competence, knowledge, and skills are crucial elements facilitating behavioral change [44]. Psycho-education looks to support the individual's understanding of a challenging situation and help gain access to resources, develop awareness of issues, foster a sense of control, and educate about coping skills for both families and their networks. These factors focus on improving cognitive awareness and coping skills. However, psycho-education also looks to promote insights that address affective worries and concerns [44]. This study focuses on investigating whether the psycho-education of social networks’ members is an appropriate method to achieve beneficial effects with respect to increasing social support and thereby parental quality of life, mental health and parental capacity, and thus the children’s well-being. Based on the theoretical framework we have developed a conceptual model of the study (Figure 1).

As shown in Figure 1, it is hypothesized that the Cancer-PEPSONE program will enhance the family’s social network support. This enhanced support will have direct effects on healthy parents’ quality of life, mental health, and parental capacity, as well as direct and indirect effects on children’s quality of life and mental health. The study upholds the child’s perspective and complies with the Norwegian Act for Health Personnel [45], putting children’s well-being on the agenda when living with parental illness. It also complies with the International Convention on the Rights of the Child (UN), emphasizing the rights of children to care, protection, rehabilitation, and assistance in various situations that can negatively affect their life situation.

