### Objectives and Hypotheses

The purpose of the Cancer-PEPSONE project is to expand the knowledge base and build competence in networks to help children living with parental cancer. The overall aim of the study is to optimize social support from the social network through a psycho-educational intervention. Based on the project’s aims and research model, we hypothesize that (1) a psycho-educational program will improve the provisions of social support to the affected family, (2) parental psychosocial health and quality of life will increase through social network support, and (3) the children’s psychosocial health and quality of life will improve because of more and better social support and increased parental capacity, mental health, and quality of life.

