### Eligibility Criteria

The study contains 3 samples. Sample 1 and 2 (n=60) consist of 30 families in the intervention group and 30 in the control group. These samples include the healthy parent and one child from each family. The inclusion criteria for these families are (1) a healthy parent having a partner or spouse diagnosed with cancer within the last five years and treated for cancer and (2) one child in every family, aged 8-18 years old, living with a parent who has cancer. With multiple children in the family, the oldest child who is willing to participate will be recruited. The parents in the intervention group ask the number of adult network members (mean 7, limited to 15 network members, N=210) if they want to participate in the intervention. This group of adult network members makes up Sample 3. The inclusion criteria for these network members are (1) extended family members, friends, neighbors, and work colleagues of the parents, (2) ≥18 years, and (3) living nearby the family.

The exclusion criteria for the study are (1) healthy parent not living with the ill parent or the ill parent has died, or having a serious disease, (2) children <8 years old, not living with ill parents, serious disease themselves, and (3) network members living >2 driving hours from the family.

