##### Power Calculations and Statistical Analyses

When comparing differences between the intervention group (n=30) and the control group (n=30), the power analysis showed that with *P*<.05 and a statistical power = .80, one would be able to detect effect sizes of *t* tests of about 0.65 of one standard deviation or higher [46]. This means an ability of detecting effects sizes of medium size or higher according to Cohen’s criteria [46]. This effect level was judged to be of clinical interest, and was within the study’s recruitment frame and economy.

All the data will be coded, verified, and entered into IBM SPSS Statistics for Windows Version 22.0. Normality will be assessed through examinations of skewness and kurtosis for all variables. A two-tailed *P* value of <.05 is considered to be statistically significant [46,57]. Descriptive statistics (mean/median or percentages, SD, and ranges) and correlation analyses (Pearson correlation) will be used to describe the data and to explore relationships among them [57]. The outcome variables will provide sum-scores on the interval level. Multiple regression analysis will be used to explore directional relationships among variables and testing the research model. For the estimation of the effect and the relationships of the variables relevant to the intervention, different methods such as *t* tests and structural equation (SEM) analyses will be used [57]. The missing data problem will be analyzed according to the questionnaires’ manual. Statistics will be reported in line with the SAMPL guidelines stated by Lang and Altman [58].

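### Hypotheses 2 and 3 are worded as causal mediation, but the sample size rests on a two-group t test and only arm is allocated, so the mechanism analyses should be exploratory

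*Protocol article*

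**What the plan says.** Objectives and Hypotheses derives three hypotheses from the research model. Hypothesis 2 has parents gaining by way of network support. Hypothesis 3 says of the children that "quality of life will improve because of more and better social support and increased parental capacity", together with better parental mental health and quality of life. The Theoretical Framework gives the same chain: the program raises network support, and "This enhanced support will have direct effects on" the healthy parent's quality of life, mental health and parental capacity, with both direct and indirect effects on two child outcomes. That section also concedes that the causal links behind social support are not settled.

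Power Calculations and Statistical Analyses states: "Multiple regression analysis will be used to explore directional relationships among variables and testing the research model". The next method sentence lists t tests and SEM together for the effect and for relationships relevant to the intervention. The only power statement is for a t test with 30 per arm, "a statistical power = .80" and an effect of "about 0.65 of one standard deviation or higher". Elsewhere the section says that "A two-tailed *P* value of <.05 is considered to be statistically significant". Under Eligibility Criteria, the parent and child samples "consist of 30 families in the intervention group and 30 in the control group".

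**The concern.** A comparison of the two arms can show whether parents and children did better when the program was offered. It cannot by itself show that they did better because support rose, or because parents coped better. Those steps relate one post-allocation variable to another. A family's severity of illness, income or temperament could move both, and allocation of arm does not balance families across levels of support.

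The sentence on regression joins exploring and testing without saying which applies to the mechanism. The number of families was not chosen with indirect effects in view. At stake is a statement that the program works through network support when the data cannot separate that from confounding, or a null mechanism result that is only low power. The Discussion says guidelines for the local healthcare system will follow if the results are successful, so the claim would be used.

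**Working it through.** **Inputs from the article.** 30 families per arm, 60 in total; one parent and one child per family; two-sided 0.05; power 0.80; detectable effect 0.65 SD; three waves (T1 before allocation, T2 at 3 months, T3 at 6 months).

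**Assumptions, because the article gives no such figures.** Arm effect on support d = 0.65 SD (range 0.5 to 0.8); later standardized paths b = 0.3 or 0.5; confounding correlation 0.1 or 0.3. Figure 1 is not shown, so the path model is read from the Theoretical Framework text.

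**1. The plan's own figure.** Detectable effect = (z for alpha + z for power) × √(2/30).
- Two-sided: (1.960 + 0.842) × 0.258 = 0.72 SD (0.74 with the t distribution).
- One-sided: (1.645 + 0.842) × 0.258 = 0.64 SD (0.65 with t).

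So 0.65 matches a one-sided test, although the plan is two-tailed. That is a separate point. What matters here is that the two-sided t test has 70% power at 0.65 SD, so the first link of any chain has 70% power, not 80%.

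**2. Power for a true mediated effect at N = 60.** Both links (three for the serial chain) must be significant, support being tested with arm in the model. For one mediator, power is close to the product of the two links. A within-arm correlation of 0.3 is detected in 65% of trials and one of 0.5 in 99%.
- b = 0.3: 0.70 × 0.65 = 0.45. Simulation: 44% to 45%.
- b = 0.5: 0.70 × 0.99 = 0.69. Simulation: 68% to 69%.
- Serial chain to the child (hypothesis 3), simulated: 26% to 27% at b = 0.3; 65% to 66% at b = 0.5.
- At d = 0.5, one mediator: 29% to 46%. At d = 0.8: 55% to 84%.

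For 80% power at d = 0.65 and b = 0.3, one mediator needs between 100 and 120 families in total and the serial chain between 120 and 140. At b = 0.5 both need about 80.

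**3. False mediation from confounding.** Set the true support-to-outcome effect to zero and let an unmeasured common cause produce a within-arm correlation between support and outcome.
- Correlation 0.3: support path falsely significant in about 65% of trials, whole chain in 0.70 × 0.65 = 0.45 (simulation 44% to 45%).
- Correlation 0.1: support path about 12%, whole chain 8% to 9%.

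The 45% equals the power for a true path of 0.3 in step 2. The test cannot tell the two situations apart, and more families would raise both rates together.

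**4. Size of an observed-score path model.** Variables: arm, one support score, three parent scores, two child scores. Parameters: arm to support 1; support to parent 3; support to child 2; parent to child 6; residual variances 6; residual covariances 3 + 1; variance of arm 1. Total 23, against 7 × 8 / 2 = 28 moments. Families per parameter: 60 / 23 = 2.6. The five spare moments correspond to the five omitted arrows from arm straight to the parent and child scores (3 + 2). On this reading, the model is testable only because it assumes that the program acts solely through support.

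**The case against.** The article does not go as far as a hurried reader might infer, in these respects.

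- **That the hypotheses will be settled by an SEM of the whole model.** The sentence on the research model names regression and speaks of exploring as well as testing. SEM appears in a different sentence, beside t tests, as one of several methods. No SEM specification is given, and a fuller plan may hold one.
- **That the model has more parameters than families.** This would follow from entering questionnaire items one by one, but the article says outcomes are sum-scores. On that reading the model is identified.
- **That support and child outcome come from one questionnaire at one time.** Children and parents answer separate questionnaires, and three waves allow some time ordering.
- **That 60 families cannot show mediation.** With strong links (d = 0.8, b = 0.5) the one-mediator test has 84% power.
- **That the between-arm comparison is displaced.** T tests are already listed for estimating the effect, and the power calculation is built on them.
- **That the trial will stop short of 60 families.** The count of 45 enrolled in October 2015 is an interim one, so 60 is used here.

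All of this stands and limits the size of the point. It does not remove it. The hypotheses are still worded as causes, the same sentence still says the model is tested, the sample size still addresses only a t test, and time ordering does not remove an unmeasured common cause.

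**Conclusion.** The concern holds in this limited form. The mechanism parts of hypotheses 2 and 3 are not protected by the allocation of arm, and 60 families support them only weakly. At d = 0.65, power is about 45% to 68% for one mediator and about 26% to 66% for the chain to the child, against the 80% the plan sets for its t test. A confounding correlation of 0.3 with no true support effect yields a false chain in about 45% of trials, and one of 0.1 in 8% to 9%. Path sizes, confounding strength and the 23-parameter count are assumptions. The lack of any power statement for indirect effects and the post-allocation status of support and parental capacity are read directly from the article. Whether parents and children improved at all remains answerable from the arm comparison.

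**What to change.** In Power Calculations and Statistical Analyses:

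1. Make T1-adjusted between-arm differences (ANCOVA, with the T1 score as covariate) in the parent and child outcomes the tests of whether parents and children improved, in place of unadjusted t tests. T1 is collected before allocation, so it is a valid covariate. For an assumed correlation r between T1 and follow-up, the detectable effect shrinks by √(1 − r²): from 0.72 SD to 0.69 (r = 0.3), 0.63 (r = 0.5) or 0.52 (r = 0.7).
2. Replace the statement that regression tests the research model with one small, pre-named, observed-score mediation analysis: arm, then support at T2, then outcome at T3, adjusted for the T1 mediator and T1 outcome, with a bootstrap 95% confidence interval. Name the support score in advance, since both the Crisis Support Scale and the Assistance Questionnaire measure it. Label the analysis exploratory and state the no-unmeasured-confounding assumption.
3. Say in the hypotheses that the routes through support and parental capacity are exploratory.

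The change is one of wording and analysis; the three waves are already planned. The price is that the mechanism parts of hypotheses 2 and 3 become exploratory. With only two follow-up waves, the longer chain from support through parent to child cannot be fully ordered in time. Nor does the change make the arm comparison strong: the t test with 30 per arm has 48% power for a difference of 0.5 SD, so a modest effect on children could still be missed.

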##### Data Collection

Healthy parents and the children fill out the entire dataset at inclusion (T1), after 3 months (approximately one months after the intervention for the intervention group), and after 6 months (Figure 2). One of the two first authors provides the families with questionnaires by post and they return them to the researchers in pre-stamped envelopes. The social network members in the intervention group fill out the T1 questionnaires prior to the meeting starting. The network members in the intervention group fill out the same questionnaires after 3 (T2) and 6 months (T3), distributed via the Internet and the website SurveyMonkey.

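### The effect analysis names t tests but no comparison adjusted for the T1 score; at 30 per arm a two-tailed t test detects 0.74 SD, not about 0.65 SD

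*Protocol article*

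**What the plan says.** The section Power Calculations and Statistical Analyses assigns methods to purposes.

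- **Effect estimation.** "For the estimation of the effect and the relationships of the variables relevant to the intervention", the article offers a list introduced as examples, in which t "tests and structural equation (SEM) analyses will be used". It does not say whether the t tests use follow-up scores or change from T1.
- **Regression.** This has another role: "Multiple regression analysis will be used to explore directional relationships among variables and testing the research model". It is not named as the treatment comparison.
- **Power.** With 30 families per arm, P<.05 and "statistical power = .80, one would be able to detect effect sizes of" t "tests of about 0.65 of one standard deviation or higher".
- **Sidedness.** "A two-tailed *P* value of <.05 is considered to be statistically significant".

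On the baseline, the Data Collection section says "Healthy parents and the children fill out the entire dataset at inclusion (T1"), with the same set repeated after 3 and 6 months. Under Trial Design, families are allocated in the order in which their consent forms and first questionnaires come back. The T1 scores therefore exist before allocation. The article gives no T1-to-follow-up correlation and no allowance for dropout.

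**The concern.** The t test is both a named method for the effect and the basis of the sample size. In its usual form, on follow-up scores, it makes no use of the T1 value of the same instrument. That value is available for each allocated family, precedes allocation, and is likely to be the best single predictor of the follow-up score. With 60 families in all, children aged 8 to 18 and diagnoses up to five years old, between-family variation can be expected to be large, and T1 would absorb part of it.

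Two things are at stake. The first is sensitivity: the article calls 0.65 SD the effect level of clinical interest, and the named test with the stated two-tailed criterion does not reach it at 80% power. The second is clarity: an open list without a defined adjusted comparison leaves the use of T1 to be settled later, possibly after the data are seen.

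**Working it through.** **Inputs.** From Power Calculations and Statistical Analyses: 30 per arm, P<.05 two-tailed, power .80, effect 0.65 in SD units. Assumed here: no dropout, and a range for the T1-to-follow-up correlation r, because the article gives neither.

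**Step 1: the article's own figure.** For a two-sample t test, df = 30 + 30 − 2 = 58 and the noncentrality is d / √(1/30 + 1/30) = d / 0.2582. At d = 0.65 this is 2.517.

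| Test | Power at 0.65 SD | Detectable effect at 80% power | n per arm for 80% power at 0.65 SD |
|---|---|---|---|
| Two-tailed .05 (as stated) | 69.7% | 0.74 SD (0.7356) | 39 |
| One-sided .05 | 80.0% | 0.65 SD (0.6496) | 30 |

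The normal approximation agrees. Two-tailed: (1.960 + 0.842) × √(2/30) = 0.72 SD. One-sided: (1.645 + 0.842) × √(2/30) = 0.64 SD. So the stated figure is reproduced only by a one-sided test.

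**Step 2: adjustment for T1.** Analysis of covariance on T1 has residual SD √(1 − r²) and df = 57. Losing one degree of freedom moves the detectable effect at r = 0 only from 0.7356 to 0.7358. The detectable effect is 0.7358 × √(1 − r²). For example, at r = 0.5 it is 0.7358 × 0.8660 = 0.637.

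**Step 3: t test on change from T1.** The SD of change is √(2(1 − r)), so the detectable effect is 0.7356 × √(2(1 − r)).

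| r (assumed) | ANCOVA: detectable effect | ANCOVA: power at 0.65 SD | Change score: detectable effect |
|---|---|---|---|
| 0.3 | 0.70 SD | 73.7% | 0.87 SD |
| 0.4 | 0.67 SD | 77.0% | 0.81 SD |
| 0.47 | 0.65 SD | 80.1% | 0.76 SD |
| 0.5 | 0.64 SD | 81.5% | 0.74 SD |
| 0.6 | 0.59 SD | 87.1% | 0.66 SD |
| 0.7 | 0.53 SD | 93.4% | 0.57 SD |

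**Step 4: correlation needed for 0.65 SD.** ANCOVA: r = √(1 − (0.65/0.7358)²) = 0.47 (0.44 by the normal approximation). Change score: r = 1 − (0.65/0.7356)²/2 = 0.61.

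**Step 5: why ANCOVA beats the change score.** The variance factors differ by 2(1 − r) − (1 − r²) = (1 − r)², which is positive for every r below 1. At r = 0.5 the change score has the same variance as the raw follow-up score (2 × 0.5 = 1), against 0.75 for ANCOVA. Below 0.5 the change score is worse than ignoring T1.

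**The case against.** The strongest reply is that the article nowhere excludes T1. Its method list is open. SEM and multiple regression can both carry a baseline score, and a t test can be run on change scores, which do use T1. An article condenses a fuller plan, and covariates are often left to an analysis plan that is not shown here.

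This stands in part. A reader might infer that the analysis will ignore T1, or that separate unadjusted tests will be run at 3 and 6 months. The text does not say either. What it does say is that t tests are a named method for the effect, and it builds the detectable effect on them. The point is therefore more than missing detail: a stated method can be replaced by a better one. Reading the t tests as change-score tests does not remove the point, since they would need r of about 0.61 to reach 0.65 SD.

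A second reply is that adjustment cannot be promised to deliver 0.65 SD. This stands in full. The correlation is unknown, may differ between instruments and between 3 and 6 months, and at 0.3 to 0.4 leaves power at 74% to 77%. Any dropout raises the correlation needed.

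A third is that baseline adjustment does not repair the allocation method. This also stands. Under Trial Design every other family goes to each arm in order of return. Adjustment handles imbalance in the measured T1 score, but it does not remove selection on unmeasured factors that predictable alternation allows.

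**Conclusion.** The point holds in limited form. No T1-adjusted treatment comparison is named although T1 is available before allocation. The stated sensitivity of about 0.65 SD is also not what a two-tailed t test with 30 per arm provides: that test detects 0.74 SD at 80% power and has 70% power at 0.65 SD.

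Covariance adjustment improves sensitivity over the unadjusted t test at each of the correlations tabulated. A reader might conclude that it simply restores 0.65 SD. The documents do not support that: it does so only if r is about 0.47 or more with all 60 families followed up.

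The figures are for a comparison at a single time point with one covariate. They do not by themselves justify a particular headline time point or further covariates such as child age or sex. They concern parents and children only, since network members are surveyed only in the intervention group.

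**What to change.** For each parent and child outcome, make the effect analysis an ANCOVA with the T1 score of the same instrument as covariate, or a mixed model of the T2 and T3 scores with that covariate. Keep t tests as supplementary.

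In the power statement, either restate the unadjusted two-tailed detectable effect as 0.74 SD, or keep 0.65 SD and state that it rests on T1 adjustment, full follow-up and an assumed correlation of at least about 0.47.

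No new families or measurements are needed, and the statistical cost is one degree of freedom. It is still a protocol change: the Ethical Implications and Risk section requires changes to be applied for to the ethics committee and the data services body. With 45 families enrolled as of October 2015 and first results expected then, it should be settled and dated before outcomes are compared by arm.

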## Methods

### Trial Design

Based on the study’s hypothesis and research questions, the Cancer-PEPSONE study will be conducted as a single center, randomized controlled trial (RCT) [46], including an intervention and a control group. This design is best suited to test the effectiveness of various types of intervention in clinical trials. The Cancer-PEPSONE study design is outlined in Figure 2.

After receiving written and oral information from one of the two first authors, families fulfilling the inclusion criteria are included in the study. The participants receive a form for informed consent and the first set of questionnaires for the healthy parent and one child in the family (T1) by mail. The consent form and the questionnaires are returned to the researchers in pre-stamped envelopes. Then, every other family is randomized to either the treatment group or the control group by one of the researchers based on the order in which the informed consent and questionnaires are returned. The type of intervention makes it impossible to blind the trial participants or the psychologist. The families in the intervention group and their network members receive the intervention, while the control group receives no intervention (care as usual). The control group is offered the intervention after finishing the study participation, after approximately 6 months, and all participating families get a DVD of the program after finishing T3 after 6 months.

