#### Ethical Implications and Risk

The Regional Committee of Research and Ethics in Western (REK West) Norway and the Norwegian Social Science Data Services (NSD) approved the research protocol October 9, 2013 (reference number: 2013/1491/REK vest).

The study will be conducted in compliance with the Declaration of Helsinki [59] and the requirements for data processing outlined in the NSD [60]. Only the two first authors have access to the data files. Procedures for handling data and data security in the study are developed. Study participation is based on written and oral information and written consent [59]. For children <12 years of age, the parents must consent on behalf of the children, whereas for the 12-18 year old children the consent is given from both parts. Study participation is voluntary and participants can withdraw at any time without the provision of reasons or any negative consequences. Serious risks or undesired effects of the intervention or the assessment by questionnaires are not described in the literature and no specific risks related to this study are anticipated. All the professionals participating in the study have extensive experience as researchers or clinicians in the field of working with children, serious illness, crisis, grief, and trauma. This competence will secure ethical and safe conditions for the participants. A referral process for further assistance or treatment for participating families with special needs will be ensured by the psychologist. Any changes in the study protocol will be applied for to REK West and NSD.

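### The only missing-data rule points to the questionnaire manuals, which can be expected to settle skipped items but not unreturned T2/T3 forms; the t tests would then rest on completers

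*Protocol article*

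**What the plan says.** In the protocol article, Power Calculations and Statistical Analyses gives one rule for missing data: "The missing data problem will be analyzed according to" the manuals of the questionnaires. No other missing-data rule appears in the article. For the intervention effect, the same section says that "different methods such as *t* tests and structural equation (SEM) analyses will be used". It names no estimator for incomplete cases and no missing-data assumption. Multiple regression is named for relationships among variables and for the research model. The power statement is framed in t tests with 30 families per arm and makes no allowance for loss.

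Data Collection sets out the follow-up: "Healthy parents and the children fill out the entire dataset at inclusion (T1), after 3 months", and again after 6 months. Families get the forms by post and "they return them to the researchers in pre-stamped envelopes". Network members, who exist only in the intervention arm, answer T2 and T3 forms "distributed via the Internet and the website SurveyMonkey". Under Ethical Implications and Risk, "participants can withdraw at any time without the provision of reasons or any negative consequences". Trial Design states that families are allocated in the order in which consent and the T1 questionnaires come back, that participants are not blinded, and that "The control group is offered the intervention after finishing the study participation", after about 6 months.

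**The concern.** The sentence addresses missing data as a whole and assigns it to documents that are written for scoring. Two kinds of missingness are involved. One is an item left blank in a returned form, where a manual can say how to build the sum score. The other is a whole T2 or T3 form that is not returned, where there is nothing to score. With postal follow-up over 6 months in families under strain, the second kind is foreseeable.

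A t test at T2 or T3 drops a family without that score and ignores its T1 score and any T2 score. If the lost families differ from those that stay, and differ more in one arm, the contrast between arms shifts. The arms do differ in what might keep a family in or lose it: one has had the meeting, the other is waiting, and both know it. At 30 per arm, even harmless loss also costs precision.

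**Working it through.** **Inputs from the protocol article.** 30 families per arm; two-tailed P<.05; power .80; stated detectable effect about 0.65 SD; assessments at T1, 3 and 6 months. No dropout rate is stated, so every loss rate below is an assumption.

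**1. The plan's own figure.** For a two-sample t test with SD 1, the detectable effect is approximately (z for alpha + z for power) × √(2/n).
- Two-tailed, n = 30: (1.960 + 0.842) × √(2/30) = 0.72; with the exact noncentral t, 0.736.
- One-tailed, n = 30: (1.645 + 0.842) × √(2/30) = 0.64; exact, 0.650.

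The stated 0.65 therefore matches a one-tailed test, while the section declares two-tailed testing. That is a separate issue. The right no-loss baseline here is 0.74 SD.

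**2. Precision lost through non-return** (equal loss in both arms, two-tailed, exact t):

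| Assumed loss | Families per arm | Detectable effect, 80% power | Power at 0.65 SD |
|---|---|---|---|
| 0% | 30 | 0.736 SD | 0.70 |
| 10% | 27 | 0.777 SD | 0.65 |
| 20% | 24 | 0.826 SD | 0.60 |
| 30% | 21 | 0.886 SD | 0.54 |

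Loss of 10% adds 0.777 − 0.736 = 0.04 SD and loss of 20% adds 0.826 − 0.736 = 0.09 SD.

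**3. Bias of a completer comparison, general form.** If a fraction d of an arm is lost and returners differ from non-returners by g SD, that arm's completer mean is off by d × g. With informative loss in one arm only and g from 0.25 to 0.8:
- d = 10%: 0.025 to 0.08 SD
- d = 20%: 0.05 to 0.16 SD
- d = 30%: 0.075 to 0.24 SD

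If d and g are the same in both arms, the errors cancel and the bias is zero.

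**4. One concrete pattern.** Assumptions: no true effect; normal scores with SD 1; T1-T3 correlation 0.6; 10% random loss in the intervention arm; control loss p confined to families above the median T1 distress. The mean of the upper half of a standard normal is √(2/π) = 0.798 and that of the lower half is −0.798. Retained controls have a mean T1 of

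[0.5 × (−0.798) + (0.5 − p) × 0.798] / (1 − p) = −0.798 × p/(1 − p).

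Multiplying by 0.6 gives the shift at T3. Random loss leaves the intervention mean at 0, so the false difference is 0.6 × 0.798 × p/(1 − p):
- p = 15%: 0.479 × 0.176 = 0.08 SD
- p = 25%: 0.479 × 0.333 = 0.16 SD
- p = 35%: 0.479 × 0.538 = 0.26 SD

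Simulation under the same assumptions gave 0.083, 0.158 and 0.258. Conditioning on T1 returned the difference to zero within simulation error (−0.001, −0.003, 0.001). That recovery holds by construction, because loss was made to depend on T1 alone. In this pattern the control arm looks less distressed than it is, so the error runs against the intervention; another pattern could reverse it.

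**5. Are the needed data available?** Allocation follows return of the T1 forms, so every allocated family should have T1 scores. A model that uses T1 and whatever follow-up exists therefore needs no new data.

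**The case against.** The strongest objection is that this is a journal article. Its analysis section is two paragraphs long, and handling of missed visits and analysis populations is commonly left to a fuller plan. The sentence comes shortly after a statement about sum scores and could be read as an item-scoring rule only. That reading is possible. But the sentence speaks of the missing data problem without limit and names one remedy, so a fuller plan would have to depart from it rather than fill it in. If the narrow reading was meant, saying so is part of the fix.

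Several further points stand and limit the concern:
- The manuals are not shown. What they cover is inferred from the purpose of a scoring manual.
- A reader might infer that the whole effect analysis will be restricted to completers. The article does not support that. The list of methods is open and includes structural equation modelling, which can keep incomplete cases through full-information likelihood. The restriction follows for the t tests and is open for the rest.
- A reader might infer that the trial's result will be biased. Nothing shows that. The pattern in step 4 is one-sided by design: control losses of 15%, 25% and 35% mean losing 30%, 50% and 70% of the more distressed control families and none of the others. The smaller two biases are also well below the standard error of the difference with no loss, √(2/30) = 0.26 SD.
- Controls are offered the intervention, and all families a DVD, once participation ends, which may encourage them to stay. The right to withdraw is standard ethics text, not evidence of attrition. The Results section accounts for all 45 enrolled families (19 + 20 + 6) and mentions no withdrawals, though it gives no T2 or T3 return rates.
- It is tempting to set 0.78 SD against the protocol's 0.65 and blame loss for the whole gap. About 0.09 SD of that gap is the sidedness issue; 10% loss accounts for about 0.04 SD.

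**Conclusion.** The concern holds in limited form. The one missing-data rule that the article states can be expected not to reach unreturned follow-up forms or withdrawals, and t tests used with it would set aside scores already collected from families lost later. Whether this biases the comparison cannot be judged from the article, which gives no dropout rate and no pattern of loss. Under the assumed pattern of step 4 the completer difference is about 0.08 to 0.26 SD, or 12% to 40% of the 0.65 SD target (0.08/0.65; 0.26/0.65). If loss is alike in both arms, the bias is zero. The precision cost does not depend on that pattern: 10% or 20% loss moves the two-tailed detectable effect from 0.74 to 0.78 or 0.83 SD. This is a weakness that is cheap to repair, not a flaw that invalidates the trial.

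**What to change.** Make four changes to the analysis section:
1. State that the questionnaire manuals govern missing items within returned forms only.
2. For the between-arm effect at T2 and T3, replace completer t tests with a likelihood-based repeated-measures model in which T1 is one of the responses, or a structural equation model with full-information likelihood. Include all allocated families, analyzed as allocated. State the assumption: the estimate is valid if loss depends only on scores already observed.
3. Report, by arm, how many T2 and T3 forms were not returned.
4. Add one sensitivity analysis by multiple imputation that includes T1, with the imputed scores of non-returners shifted by arm-specific amounts, to show how far the conclusion depends on that assumption.

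The cost is modest: a change of effect model, one additional analysis, and reliance on a missing-at-random assumption in the main analysis, which step 4 probes but cannot verify. No new families or measurements are needed. By the article's own account, enrollment was still under way in October 2015 and T3 collection was to run into spring 2016, so the change could be made before data collection ended. The model does not recover all the lost precision; it uses what has been collected.
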